**Study aim and objectives**

The overall aim will be to train at least eight clinicians in BA using an established University accredited online “Professional Certificate in BA for Depression” program and support them to deliver BA to improve depressive symptoms in YPEEP. Specifically, the objectives of the pilot trial are to:

1. Establish the proportion of YPEEP with clinically meaningful depression symptoms.
2. Establish the proportion of clinicians that complete the BA training and are deemed to be competent.
3. Determine the proportion of eligible participants approached who agree to consent to the research.
4. Determine the proportion of participants that complete baseline measures, complete BA treatment (attending for a minimum of six sessions over the six weeks), and complete follow-up measures (immediately post intervention and at 3 months follow-up).

Additionally, we will:

1. Establish clinicians’ fidelity to treatment.
2. Calculate preliminary efficacy of BA on clinical outcome measures.
3. Explore participants’ experiences of facilitating BA (clinicians) and receiving BA (YPEEP).

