**Preliminary intervention effects (primary and secondary outcomes)**

The primary outcome will be the assessment of depressive symptoms. The secondary outcome will be the assessment of negative symptoms, overall psychiatric symptoms, medication side effects, and functioning. Outcome measures will be completed at baseline (0 weeks), immediately post-intervention (6 weeks) and 3-months post-intervention.

Depressive symptoms: The depressive symptoms will be measured with Calgary Depression Scale for Schizophrenia (CDSS) [30]. The CDSS is a 4-point Likert type scale (0, absent; 1, mild; 2, moderate; 3, severe) with nine items. It is considered to be a reliable scale, with high internal consistency (Cronbach's alpha= 0.855), and the CDSS is suitable for evaluating symptoms of depression in people at clinical high risk for psychosis [31], including young people [32].

Negative symptoms: The Scale for Assessment of Negative Symptoms (SANS) [33] will be used to assess the negative symptoms of schizophrenia. SANS is 6-point Likert type scale (from 0, none to 5, severe), comprised of five scales each of which assess aspects of negative symptoms; alogia, affective blunting, avolition-apathy, anhedonia-asociality, and attentional impairment. The SANS has demonstrated a high level of reliability, with an overall Cronbach’s alpha ranging from 0.89 to 0.95 and global intraclass correlation coefficient (test-retest reliability) of more than 0.82 in different studies [33-35].

Psychiatric symptoms: The Brief Psychiatric Rating Scale (BPRS) [36] is a 7-point Likert type scale (1, not present-7, extremely severe) which is used to rate psychiatric symptoms such as anxiety, depression, and psychoses. The BPRS has demonstrated good reliability, with overall Cronbach’s alpha value of 0.69 [37] and an overall intra-class correlation of R = 0.78 (p< 0.001) [38].

Medication side effects: The Glasgow Antipsychotic Side-effect Scale (GASS) [39] is 4-point Likert type scale (from 0 point, never to 3 point, everyday) containing 22 items. It is a self-report rating scale which measures an individual’s viewpoint about side effects of antipsychotic medication. The GASS has demonstrated a good test-retest reliability (kappa value=0.72) [39] and internal consistency reliability with Cronbach's alpha ranging from 0.793 to 0.903 [40-42].

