**Data analysis**

*Qualitative data analysis*

Qualitative interview data will be content analysed from a phenomenological perspective following Braun and Clarke’s thematic analysis procedure [46]. The planned analysis encompasses the processes of immersion in the data set, line by line coding so to generate a set of preliminary codes, the development of tentative themes, reflection upon and revision of themes as needed before defining and describing finalised themes. The analysis will be inductively-oriented and data-driven. Codes and themes will be validated by an independent researcher at key points in the analysis. NVivo Pro software version 12 will be employed to facilitate the analysis.

*Statistical analyses*

Raw data will be entered and analysed with SPSS (the Statistical Package for the Social Sciences) for Windows, version 26. The demographic characteristics and baseline data measure (mean scores) of all participants will be compared between the two study groups, using Chi-squared test or independent samples t-test to assess the homogeneity of the two groups. The generalized estimating equation (GEE) will be employed to analyse the preliminary effects of BA across the three points (baseline, and 6-weeks and 3-months after intervention) following the intention-to-treat principle, and relevant effect sizes will be calculated. The GEE analysis will account for intra-correlated repeated outcome data and accommodate data missing at random. Feasibility data will be summarized with descriptive statistics. T-tests will be carried out to examine any significant statistical differences between the two arms on primary and secondary outcome measures at both follow-up measurements if the statistical significance of the overall treatment effect was found in the GEE analysis. We will also conduct Chi-squared test or independent samples t-tests (depending on normality of data) to assess significant differences in baseline data measures between participants that discontinue the study and those that adhere to the study protocol/com. In all tests, the level of significance will be set at P values of < 0.05.

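### The protocol tests all five clinical outcomes at P < 0.05, secondaries on the same footing as the CDSS, in a pilot it calls preliminary and unpowered for such tests (minor)

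*Protocol*

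**What the plan says.** The Protocol names one primary clinical outcome: "The primary outcome will be the assessment of depressive symptoms", measured with the CDSS. It then names four more: "The secondary outcome will be the assessment of negative symptoms, overall psychiatric symptoms, medication side effects, and functioning", measured with the SANS, BPRS, GASS and WSAS.

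Under Data analysis, "The generalized estimating equation (GEE) will be employed to analyse the preliminary effects of BA across the three points". A second step follows: "T-tests will be carried out to examine any significant statistical differences between the two arms on primary and secondary outcome measures at both follow-up measurements", but only "if the statistical significance of the overall treatment effect was found in the GEE analysis". The section closes with one level for everything: "In all tests, the level of significance will be set at P values of < 0.05".

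Other sections set a more modest purpose. Study aim and objectives lists "Calculate preliminary efficacy of BA on clinical outcome measures" among the additional objectives, after four feasibility objectives. The Sample size section says that 60 participants (30 per group) should help plan a later full-scale trial, and that the number was not chosen to give adequate power for between-group significance.

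**The concern.** The testing rule does not match the stated purpose. A study that disclaims power for between-group comparisons makes significance at 0.05 the criterion for what is called a difference, and for whether the two follow-up time points are compared at all.

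The rule is also the same for the primary and the secondary outcomes. Calling the CDSS primary has no effect on the testing: a secondary outcome can be reported as significant, under the same sentence, when the CDSS is not.

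The results are to be published and are meant to inform a full trial. With five outcomes and a flat 0.05 rule, an isolated positive result on, say, functioning or negative symptoms is a realistic chance event. The plan gives the reader no statement that such a result should be read differently from one on the CDSS.

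**Working it through.** **Plan's own figure.** The Protocol states no family-wise error rate and no power, so there is none to reproduce. The related number is the sample size, 2 × 30 = 60, which rests on literature guidance for feasibility studies and not on a power formula.

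**Inputs from the Protocol.**
- Level 0.05 for every test (Data analysis). Sidedness is not stated; two-sided is assumed here.
- Five outcomes: one primary plus four secondary (Preliminary intervention effects).
- One overall GEE test per outcome, then t-tests at two follow-ups if the GEE result is significant (Data analysis).

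**Assumed input.** The Protocol gives no correlation between outcomes. A common correlation between the five test statistics is therefore varied from 0 to 0.9.

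**Step 1: at least one of five significant when BA has no effect.** If independent: 1 − 0.95^5 = 0.226. For positive correlation, five equicorrelated normal test statistics were simulated (1,000,000 draws, two-sided 0.05).

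**Step 2: a significant secondary with a non-significant CDSS.** The CDSS alone is significant with probability 0.05, so this is P(any of five) − 0.05. Direct check under independence: 0.95 × (1 − 0.95^4) = 0.95 × 0.1855 = 0.176, which equals 0.226 − 0.05.

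| Assumed correlation | At least one of five | Secondary significant, CDSS not |
|---|---|---|
| 0 | 22.6% | 17.6% |
| 0.3 | 20.9% | 15.9% |
| 0.5 | 18.3% | 13.3% |
| 0.7 | 14.8% | 9.8% |
| 0.9 | 10.2% | 5.2% |

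**Step 3: the follow-up t-tests.** They run only after a significant GEE result. The Protocol does not say whether that condition applies outcome by outcome. Read that way, they add no outcome with a false-positive finding, so they do not enter the table.

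**Step 4: sensitivity to the 5% itself.** The table assumes that each GEE test holds its nominal level. In a simulation with 30 per arm, complete data, within-person correlation 0.5, a saturated group-by-time model and a two-degree-of-freedom robust Wald test without small-sample correction (3,000 runs per setting), each test rejected about 6.7% to 7.0% of the time. At least one of five then rejected in about 20% (correlation 0.7) to 30% (correlation 0). The Protocol does not fix the model in this detail, so the conclusion does not rest on this step.

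**The case against.** The strongest reply is that the plan already treats these analyses as non-confirmatory. It names one primary outcome, calls the effects preliminary in the objectives, the outcome section heading and the analysis text, plans effect sizes and disclaims power. A per-test level of 0.05 is not a promise of family-wise control, and multiplicity is often handled in a statistical analysis plan, which is not at hand.

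Much of this stands, and it rules out several stronger readings that a reader might infer:

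- *That outcomes have no hierarchy.* They do: one is primary and four are secondary. What is absent is any consequence of that ranking in the testing rule.
- *That nothing marks the analyses as non-confirmatory.* The word exploratory is not used for them, but preliminary is, repeatedly.
- *That the trial breaches an error rate it claims.* No family-wise rate is claimed, and the CDSS test carries its nominal 5%.
- *That 18% is a property of this trial.* It needs an assumed correlation of 0.5; only the range can be defended.
- *That the five SANS scales mean nine tests.* Negative symptoms are listed as one outcome, and nothing says that the scales will be tested separately.
- *That ten t-tests inflate the error further.* Read per outcome, the GEE condition prevents this.
- *That a chance secondary result will choose the next trial's endpoint.* No rule in the Protocol makes any decision depend on a secondary P value.

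The reply does not dispose of the testing rule itself. The 0.05 sentence and the search for significant differences on secondary outcomes are written into the Protocol, so this is not detail left open for later. An analysis plan that made the secondary P values descriptive would have to depart from that text. The preliminary wording sits in the same paragraph as the rule and does not qualify it.

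**Conclusion.** The point holds as a minor one: the significance rule in Data analysis fits poorly with the purpose set out under Sample size, and it gives secondary outcomes the same claim to significance as the CDSS.

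If BA has no effect, at least one of the five outcomes would be nominally significant with a probability of about 10% to 23%, that is, about 2 to 4.5 times the 5% carried by the single primary outcome. A significant secondary beside a non-significant CDSS would occur with a probability of about 5% to 18%. These ranges assume two-sided tests at their nominal level, one overall test per outcome and a common between-outcome correlation from 0.9 down to 0.

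The documents do not support saying that the primary comparison is inflated or that any design decision hangs on a secondary result. The risk lies in how isolated results are described and read.

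**What to change.** In Data analysis, add that the clinical-outcome analyses are exploratory. Then replace the conditional t-test sentence with a commitment to report between-arm differences with 95% confidence intervals at both follow-ups for all five outcomes, whatever the GEE result. Make no significance claim for the SANS, BPRS, GASS or WSAS. If a nominal 0.05 level is kept for any outcome test, confine it to the CDSS and describe it as preliminary.

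The existing 0.05 sentence also governs the baseline comparison of the groups and the comparison of participants who discontinue with those who adhere. The new wording should therefore be limited to outcome tests, so that those comparisons are not left without a level.

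Formal gatekeeping with adjusted P values is not needed. It would place the side-effect scale behind an efficacy result in a study not powered for efficacy.

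The cost is about two sentences, with no new data and no change in sample size. The one downside is that an isolated secondary result can no longer be called significant.

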**Dissemination**

The Consolidated Standards of Reporting Trials (CONSORT) framework [47] (Figure 2.) will be followed when reporting the present pilot trial findings.

Fig 2. CONSORT framework for reporting

[figure not shown]

The findings of the study will be written up and submitted for publication. Authorship of any publications will be determined using the recommendations by International Committee of Medical Journal Editors concerning authorship. Findings will also be presented at relevant scholarly and professional conferences. Additionally, the participating study sites will be informed of the report so that they may distribute copies of the report to participants, if desired. Public access to the study protocol will be ensured via the publication of the protocol in a professional peer-reviewed journal and registration of the trial protocol in a publicly accessible database.

**Ethical approval**

Ethical approval for the study has been granted by the Charles Darwin University Human Research Ethics Committee (ref no. H22003) and the appropriate ethical approval/governance approvals will be obtained from the early psychosis service at the study site. Potential participants will be aware that their participation is entirely voluntary and that they may withdraw from the study at any point without penalty. Participants aged <18 years will also need to provide parental/guardian consent to take part in the study. Recruitment will be conducted by a trained research assistant who is not working at the service provider in order to minimise the risk that participants may feel coerced to take part (please see “Recruitment” section for more detailed information).

The intervention will be delivered by the YPEEP participant’s regular clinician who will be responsible for recognizing, responding and reporting any distress arising from the intervention (i.e. debriefing). After each YPEEP participant has completed each session of BA, the clinician will ask them about their emotional well-being and if they have experienced any distress. If distress is experienced, the participants will have access to ongoing support through their existing clinical/support team and will be aware of how to contact this team. Approval will be sought for any modifications to the protocol from the ethics committees noted above and amendments will be made to the documentation submitted to the Australian New Zealand Clinical Trials Registry, accordingly.

**Patient and public involvement**

A youth advisory committee was consulted to develop and refine the study recruitment materials. The committee provided input to help ensure that the texts were clear and in the best possible format for young people who are attending the service to engage with. All of the suggestions from the committee were implemented. An expert by experience consultant who has lived experiences of psychosis will join the trial steering committee, in order to facilitate consumer input and guidance in this forum.

**Safety considerations**

As noted, BA has not been conducted in YPEEP before. Thus, safety considerations are formulated on the basis of studies conducting similar interventions and/or those using psychosocial interventions with the same patient population. An RCT study investigating cost-effectiveness of BA compared with CBT for adults with depression reported that depression-related, but not treatment-related, serious adverse events occurred in three participants in the BA group and eight participants in the CBT group [27]. We considered that low intensity CBT for psychosis is very similar to BA as it adopts behavioural interventions in conjunction with graded exposure [48]. A systematic review of low intensity CBT for psychosis in adults including 10 studies reported that that the intervention seemed safe (no mention of adverse events) and shows promise for psychotic symptoms [49]. The individual study most similar to our study is a pilot study of low intensity CBT for psychosis, in which the main elements of the intervention included BA and graded exposure [48]. The small study reported that staff and participant satisfaction was high, with no adverse events reported. Therefore, based on the best available evidence, a reasonable conclusion is that BA for young people with early psychosis is likely to be broadly safe and acceptable.

In order to mitigate the risk of adverse effects we will put in place several procedures. We will ensure that researchers and clinicians engage with participants at each assessment or at the start of each BA session to check how they are feeling and if they experienced any unexpected effects of the intervention. The BA will be also be delivered by participants’ routine community-based clinician, thus if the participants show any signs of suicide/self-harm risk they will be able to activate their existing risk management plan to ensure the person is supported and referred on for additional treatment as required. In addition, we will apply Good Clinical Practice best practice advice about recording and coding adverse events. All adverse events will be reported to the trial steering committee. If the trial steering committee considered that adverse events are directly associated with the intervention, we will halt the trial as appropriate.

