**Intervention**

*BA Intervention group*

Participants in the intervention group will receive BA treatment in addition to standard care. These participants will be offered 12 sessions of BA, which will be delivered twice weekly, in 30-minute sessions, for six weeks. Participants will be deemed to have received an adequate ‘dose’ of the intervention if they have attended 6 BA sessions over the 6-week period (i.e. 50%). The BA treatment will follow a treatment protocol based on previous trials of BA for depression [26], the COBRA trial protocol [27] and the National Institute for Health and Care Excellence recommendations for the frequency and duration of BA therapy [28]. Specific BA techniques that will be applied include the: identification of depressed behaviours; analysis of the triggers and consequences of depressed behaviours; monitoring of activities; development of alternative goal-orientated behaviours; scheduling of activities; and the development of alternative behavioural responses to rumination.

*TAU group*

Every participant in the control group will receive routine standard early intervention in psychosis services and no other specific intervention will be provided. Across sites, TAU is composed of case management and antipsychotic medication. Additionally, TAU may involve family support, psychosocial groups, vocational support, peer support as well as care for physical health. Multidisciplinary teams responsible for delivering standard care services usually consist of psychologists, psychiatrists, mental health nurses, occupational therapists, and social workers. The TAU condition will ensure appropriate, ongoing quality care for this group of young people. Young people at UHR status should receive care for at least 12 months and those with FEP for two years [22].

*BA training*

Eight clinicians will be recruited and trained to deliver the intervention. Each clinician will deliver the intervention to approximately five YPEEP participants. The clinicians will be trained in BA techniques using an academically accredited and established online “Professional Certificate in BA for Depression” program offered by the University of South Australia (facilitated by MJ and SD). The 10-week online training consists of five modules (the evidence base of BA; introduction to BA; assessment and mood monitoring; functional analysis; and activity scheduling).

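### Adverse events are asked about far more often in the BA arm than in the TAU arm, so raw counts by arm are not comparable and the steering committee's control information is weakened

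*Protocol*

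**What the plan says.** Four parts of the protocol together set the enquiry schedule.

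- **Safety considerations.** The safety enquiry by research and clinical staff takes place "at each assessment or at the start of each BA session to check how they are feeling and if they experienced any unexpected effects"; the effects meant are those of the intervention. The same section adds: "All adverse events will be reported to the trial steering committee". It ties halting the trial to a judgement: "If the trial steering committee considered that adverse events are directly associated with the intervention".
- **Ethical approval.** A second check applies to BA only: "After each YPEEP participant has completed each session of BA, the clinician will ask them about their emotional well-being", and about any distress.
- **Intervention.** On the BA arm: "These participants will be offered 12 sessions of BA, which will be delivered twice weekly, in 30-minute sessions, for six weeks". Six attended sessions count as an adequate dose. TAU consists of case management and antipsychotic medication, with other supports possible. No contact frequency and no adverse-event enquiry between assessments is stated for TAU.
- **Preliminary intervention effects.** Both arms share the assessments: "Outcome measures will be completed at baseline (0 weeks), immediately post-intervention (6 weeks) and 3-months post-intervention".

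The section on random allocation and blinding adds that clinicians and research assistants are not masked to allocation.

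**The concern.** How many non-serious events are recorded depends on how often, and in what words, people are asked. Here the arms differ on both. BA participants are asked at every session as well as at the assessments, and the clinician who delivers the therapy is among those asking. TAU participants have a scheduled enquiry only at the assessments, and part of it asks about effects of an intervention they did not receive.

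At stake is the meaning of any view of adverse events by arm. In young people with psychosis and depressive symptoms, some distress and worsening can be expected without BA. The TAU arm is the trial's only concurrent evidence on that background. If it is collected much more sparsely, an excess in BA may reflect detection, and a real difference cannot be separated from detection. The protocol says BA has not been used in this population before, so comparable in-trial information is worth having. TAU events that were never elicited cannot be recovered by any later analysis.

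**Working it through.** **Inputs from the protocol**

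- BA sessions offered: 2 per week × 6 weeks = 12, as stated (Intervention).
- Adequate dose: 6 sessions, and 6/12 = 50%, as stated (Intervention).
- Assessments after randomisation: 2, at the end of treatment and 3 months later (Preliminary intervention effects). The section on data collection words the timing of the first one differently, but the count of two is the same.
- Enquiry at assessments in both arms and at session starts in BA (Safety considerations).
- Post-session check in BA only (Ethical approval).

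**Scheduled enquiries per participant after randomisation**

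| | BA | TAU | Ratio |
|---|---|---|---|
| 12 sessions, session starts + assessments | 12 + 2 = 14 | 2 | 7:1 |
| 6 sessions, session starts + assessments | 6 + 2 = 8 | 2 | 4:1 |
| 12 sessions, adding post-session checks | 24 + 2 = 26 | 2 | 13:1 |
| 6 sessions, adding post-session checks | 12 + 2 = 14 | 2 | 7:1 |

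The first two rows are the fair count. A post-session check follows the pre-session one by about 30 minutes, so it adds little as a separate chance of detection.

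**Illustration of the effect on recorded events**

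The protocol gives no event rate or recall figure, so this part rests on assumptions:

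- true event rates are equal in the two arms;
- events are spread evenly over time;
- an event is recorded at the next scheduled enquiry with probability exp(−gap/τ), where τ is a recall constant in weeks;
- all 12 sessions are attended, half a week apart;
- TAU events are captured only at assessments.

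For events in an interval of length g that ends in an enquiry, the expected captured time is τ(1 − exp(−g/τ)). Summing over intervals and dividing by the period gives the fraction captured.

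Over the 6 treatment weeks:

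- BA fraction = 12 × τ(1 − exp(−0.5/τ)) / 6
- TAU fraction = τ(1 − exp(−6/τ)) / 6

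Over about 19 weeks (6 + 13, taking 3 months as 13 weeks), τ(1 − exp(−13/τ)) is added to the captured time in both arms and the divisor is 19.

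| τ (weeks) | BA, 6 wk | TAU, 6 wk | Ratio | BA, 19 wk | TAU, 19 wk | Ratio |
|---|---|---|---|---|---|---|
| 2 | 0.885 | 0.317 | 2.8 | 0.385 | 0.205 | 1.9 |
| 4 | 0.940 | 0.518 | 1.8 | 0.499 | 0.366 | 1.4 |
| 8 | 0.969 | 0.704 | 1.4 | 0.644 | 0.560 | 1.15 |
| 26 | 0.990 | 0.893 | 1.1 | 0.851 | 0.820 | 1.04 |
| perfect recall | 1 | 1 | 1.0 | 1 | 1 | 1.0 |

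Worked line, τ = 2 over 6 weeks: BA = 12 × 2 × (1 − e^(−0.25)) / 6 = 0.885. TAU = 2 × (1 − e^(−3)) / 6 = 0.317. Ratio = 2.8.

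**Sensitivity to attendance.** With 6 sessions one week apart, the BA fraction over 6 weeks is τ(1 − exp(−1/τ)), which is 0.787, 0.885 and 0.940 for τ = 2, 4 and 8. Divided by the TAU fractions above, the ratios are 2.5, 1.7 and 1.3. Half attendance therefore reduces the imbalance only a little.

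**The case against.** The strongest case against is that nothing in the protocol rests on comparing event counts. Adverse events are not among the feasibility, primary or secondary outcomes, and the statistical analyses section plans no between-arm test of them. The one safety decision is the steering committee's attribution of events to the intervention, with no rate or threshold. Close enquiry around sessions helps that judgement by giving timing and context, and it protects participants. The statement that BA is likely to be broadly safe rests on outside studies. All of this stands. A reader might infer that the trial's safety judgement cannot be made at all. The documents do not support that, because attribution can proceed case by case.

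A reader might also infer that BA counts are certain to be inflated, or take 26 against 2 as the size of the problem. Neither holds. Serious events would probably surface in either arm. TAU includes case management, all adverse events are to be reported whichever arm they arise in, and the ratios fall towards 1 as recall improves. The figure of 26 counts near-duplicate checks.

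Two further objections hold in part. First, the enquiry also covers how participants are feeling, which a TAU participant can answer. That is so, but the part on unexpected effects remains tied to the intervention. Second, the layout of by-arm tables can be left to a statistical analysis plan. The layout can, but who is asked, when and in what words is data collection, and the protocol fixes it. The Glasgow side-effect scale is given on the same schedule in both arms, but it covers medication side effects and does not fill the gap.

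**Conclusion.** The point holds as one of unequal ascertainment. The scheduled enquiry is 14 against 2 at full attendance and 8 against 2 at the adequate dose, with post-session distress checks in BA only and a question that partly does not fit TAU. These counts follow directly from the protocol.

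Recorded non-serious events are likely to be higher in BA even under equal true rates. How much higher cannot be fixed from the document. The illustrative ratios run from 1.4 to 2.8 over the treatment weeks and from 1.15 to 1.9 over about 19 weeks, for recall constants of 8 down to 2 weeks. They assume full attendance and no TAU capture between assessments. Routine TAU contact of unknown frequency would narrow them.

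Two consequences follow. Raw event counts by arm should not be compared. The background information that TAU can offer the steering committee is weaker than it need be, though not absent. Because collection in TAU cannot be repaired afterwards, the change is worth making before data are gathered.

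**What to change.** At the post-intervention and 3-month assessments, have the research assistant ask both arms the same neutral question: any new or worse health or emotional problem since the last visit, with no reference to the intervention. State that any by-arm adverse-event summary, including one shown to the steering committee, uses events from these common enquiries. List events found only through BA sessions separately and label them as such. The scheduled enquiry behind the by-arm summary is then 2 against 2.

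The session checks and the reporting of all events to the steering committee stay unchanged.

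The cost is one form item at visits both arms already attend, and a sentence on reporting. The downside is that the by-arm table will show fewer BA events than were recorded in total, which the separate listing covers. Research assistants remain unmasked, so the change equalises the schedule and wording but does not remove all reporting bias.
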